# *On your feet*: protocol for a randomized controlled trial to compare the effects of pole walking and regular walking on physical and psychosocial health in older adults

**DOI:** 10.1186/1471-2458-14-375

**Published:** 2014-04-17

**Keywords:** Pole walking, Older adults, Health

## Abstract

**Background:**

Physical activity is associated with better physical and mental health in older adults. Pole walking is a form of walking which may have additional health benefits in older adults, because of the addition of hand held poles, and consequent upper limb involvement. However, few studies have examined the potential additional effects of pole walking on physical and psychosocial health in older adults compared with walking. The aim of this study is to compare the effect of a pole walking program with the effects of a walking program, on physical and psychosocial wellbeing, in older adults in assisted living facilities.

**Methods/Design:**

Sixty men and women from assisted living communities over 65 years will be recruited from senior retirement facilities and randomized into a group based, pole walking program, or walking program. The pole walking group will use the Exerstrider method of pole walking. Total duration of the programs is 12 weeks, with three sessions per week, building from 20 minute to 30 minute sessions.

The primary outcome is physical function, as measured by items from the Seniors Fitness Test and hand grip strength. Secondary outcomes include, physical activity levels, sedentary behaviour, joint pain, and quality of life. All outcomes will be assessed before and after the programs, using valid and reliable measures.

**Discussion:**

The study will add to the evidence base for the effects of pole walking, compared with walking, on physical and psychosocial health and physical function, in healthy older adults. This will improve understanding about the feasibility of pole walking programs and its specific benefits in this population.

**Trial registration:**

Australian New Zealand Clinical Trials Registry
ACTRN12612001127897.

## Background

Being physically active is associated with better physical and mental health in adults, and it is well documented that there is no age limit to health benefits related to regular physical activity (PA)
[1]. Regular PA leads to improvements in cardiorespiratory fitness, muscle strength, endurance and flexibility
[2]. It is also associated with a decrease in the overall burden of disease, as well as improvements in psychological wellbeing, quality of life and cognitive functioning
[2,3]. In older adults, there is now good evidence that regular PA increases average life expectancy and reduces disability
[4,5]. PA which incorporates specific strength, flexibility and balance training, is also associated with a reduction in the risk of falls in this age group
[6,7].

Australian PA guidelines for older adults recommend accumulation of at least two and one half hours of moderate intensity PA on most, preferably all, days of the week for health benefits
[8]. US guidelines for older adults add that some PA is better than none, and that older adults who participate in any amount of PA will gain health benefits
[5,9]. However, PA participation among older adults is low
[10-12]. For example, of Australians aged 65–74 years, only one in three met PA guidelines in 2007–8, and the proportion was just over one in five in those over 75 years
[13]. The proportion of adults aged over 65 years is expected to increase from 13% of the total Australian population in 2007 to between 23% and 25% in 2056
[10]. Consequently, there will be a significant increase in the number of older adults who could potentially obtain health benefits from regular participation in PA. It is therefore important to find feasible ways for older adults to increase their PA levels.

Walking is one PA option for older adults, as it can be undertaken regardless of age, health status, and ability
[14,15]. It is the most frequently reported form of PA in this population group
[16,17]. For example, data from the US Behavioural Risk Factor Surveillance System (BRFSS) show that 44% of men, and 45% of women, aged over 65 years, reported leisure time walking in 2000
[18]. In addition, walking is the most frequently reported activity among older adults who meet the US PA guidelines/recommendations
[18]. In Australia, walking for leisure is reported by 46% of adults over 65 years, and of those, 53% engage exclusively in walking
[17]. Walking at, or above, 3–4 km per hour is categorized as moderate intensity PA
[19], and confers health benefits when recommended frequencies and durations are adhered to.

Pole walking (PW) is an outdoor, non-competitive activity. It is a form of walking, with the addition of hand-held poles, which utilizes upper body muscles
[20]. It has similar low impact, moderate intensity characteristics to walking
[21]. There are several additional effects of PW compared with moderate intensity walking. During PW, the average oxygen uptake, heart rate, and caloric expenditure are higher than for walking at the same speed
[21-23]. Importantly, these additional benefits are achieved without significantly increased perceived exertion
[22,24-26]. Evidence of a reduction in knee joint loading when PW is ambiguous
[27-29], although some studies have shown lower knee joint forces in participants who walk with poles than in those who don’t
[30,31]. The use of poles may provide extra stability for walkers and reduce falls or fear of falls. However, to our knowledge, no studies have measured balance and stability during PW. Because of these characteristics, PW appears to be a suitable form of PA for older adult populations.

PW is used in PA programs by community and government organisations in several countries, and many participants in these programs are older adults
[32-34]. For example, 44% of older Polish sport and recreation session participants at Universities of the Third Age attended PW sessions
[32]. A recent systematic review of the effects of PW on health found a number of randomized controlled trials of the effects of PW in a range of both clinical and non-clinical populations
[35]. These include middle aged, non-obese women
[36], adults with type 2 diabetes
[37,38], cardiovascular disease
[24], peripheral artery disease
[39,40], musculo-skeletal conditions
[41,42], chronic obstructive pulmonary disease
[43], Parkinson’s disease
[44,45], Sjogren’s syndrome
[25] and breast cancer
[46]. Most of these intervention studies lasted between 8 and 24 weeks, were of moderate intensity, and conducted 2–3 times per week
[35]. This found that PW is simple, feasible, and effective, and has several beneficial physical and psychosocial effects in mid to older aged adults
[35].

There are a number of different PW techniques. The Nordic walking technique, which emerged from the sport of cross country skiing, is practiced and taught throughout the world
[47]. In the United States, another style of PW, known now as the Exerstrider method, has developed separately from Nordic walking in Europe
[48]. The Nordic walking technique uses a longer stride length and greater hip range of motion than regular walking, and a grasp/release hand grip. The Exerstrider method uses a normal gait, a high forward arm position, and a continuous hand grip. There are indications that the Nordic walking technique is more difficult for older people than Exerstriding
[45,49]. For example, Figard-Fabre et al. found that, in obese mid-aged women, after four weeks of Nordic walking training, fewer than 50% of the participants were able to grasp three of the eight technical characteristics of the technique
[49]. In another study of adults with Parkinson’s disease, many participants had difficulties with the Nordic walking technique
[45]. These difficulties may also be experienced by older adults, who have shorter stride length, and smaller hip joint range of motion than younger adults
[50].

Although PW seems to be a suitable form of PA for older adults, few studies have examined the effects of PW on physical and psychosocial health in exclusively older adult populations
[35]. To our knowledge, only one study has examined the effects of PW in healthy adults aged over 65 years
[51]. This study found significant improvements in functional capacity, but not in gait parameters, or walking speed, in older adults who walked twice weekly for nine weeks, compared with a non-exercise control. In addition, few studies have compared the effects of PW with regular walking (RW) in older adults
[51,52]. Therefore, the aim of this trial is to compare the effects of PW with the effects of RW, on physical function, physical activity and sitting time, and wellbeing, in adults aged 65 years or over. The null hypothesis is that there is no difference in these outcomes between participants in the PW group and the RW group.

## Methods/Design

### Design

An overview of the study design and timeframe is found in Figure 
1. The study is a randomized controlled trial with two arms: a PW program; and a RW program. The study protocol was approved by the Research Ethics Committee at The school of Human Movement Studies, The University of Queensland.

**Figure 1 F1:**
[figure not shown]
**Overview of study design and timeframe.** (PW = pole walking; RW = regular walking; n = number; SF12 = 12 Item Short-Form Health Survey).

### Study sample and recruitment

Participants will be recruited from four senior living facilities at different locations, but with similar environmental characteristics. The lead researcher will initially contact management staff in the senior living facilities by phone. This phone contact will be followed by a personal visit to the facility managers to introduce the study and the lead researcher. An “Active Aging” presentation will then be offered to the residents of the villages. The presentation will consist of information about the benefits of PA for older adults. The study will be explained in detail and an opportunity for attendees to ask questions and register their interest in participating will be given at the end of the presentation. All attendees will be given an information brochure about the study and the eligibility criteria.

People interested in participating will be contacted personally by the lead researcher. She will then provide any additional information and explanations participants may require, and will screen potential participants for eligibility. Inclusion criteria are: aged 65 years or older. Exclusion criteria include: medically unfit to participate in a walking program; unable to speak or understand English; having a shoulder or elbow flexion range of motion (ROM) of less than 90 degrees; and having pathological conditions of the upper extremity.

In addition to specific verbal or written questions to check the eligibility criteria, the lead investigator will use the Sports Medicine Australia (SMA) pre-exercise screening tool to ascertain medical eligibility to participate in the moderate intensity PA programs
[53]. Written informed consent from the participants will be obtained prior to the start of the study.

### Sample size

There are no previous data on the effects of PW compared with RW on physical function and psychosocial health. Sample size estimates were therefore based on the premise that the PW group would achieve changes at least 20% greater than those observed in the RW group, in selected measures of the Seniors Fitness Test (30-second chair-stand test, 30-second arm-curl test, timed up and go test, and a 6-minute walk test)
[54]. This difference is thought to be a clinically relevant difference in functional status
[52]. Of those subtests, the largest number of participants needed for a stastistically significant 20% difference was for the arm curl test. Based on a 20% difference in normative data for women aged 65–69 years for the arm curl test (mean, 17, SD, 4.1), a power of 0.80 and significance of 0.05, and using the formula n = 2[z*s^2^/Δ^2^], we estimate that 23 participants per group would be needed to detect a between group difference of 20% (i.e. mean, 3, SD, 4.1) in the change score
[52].

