### Randomization

After baseline assessment of eligible participants at one site, the lead researcher will notify an external researcher of the participant identification numbers. The external researcher will randomly assign 50% of the participants to the PW intervention and 50% to the RW intervention using a random number generator in SPSS and inform the lead researcher of group allocation. This process will be repeated for each site separately. Thus, the total number will be approximately 30 participants in the PW group and 30 in the RW group, with one PW group, and one RW group, with seven to eight participants in each group, at each of four sites.

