#### Data analysis

To ensure that randomization resulted in equal distribution of sample characteristics in both intervention groups, baseline characteristics in the intervention and control groups will be compared using t-tests for normally distributed continuous data, appropriate non-parametric tests for non-normally distributed continuous data and chi square tests for categorical variables. Between group differences in study outcomes will be examined using repeated measures of covariance (ANCOVA), adjusted for variables that are associated with both the explanatory and outcome measures; based on previous publications, these may include factors such as age, sex and number of medical conditions.

Both intention to treat analysis, including all participants who were enrolled in the study, and provided both baseline and follow up data, and per protocol analyses, including only participants who completed the program, will be analysed. The level of significance will be set at 0.05. All analyses will be conducted using SPSS version 20 (SPSS Inc, Chicago, IL).

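### The sample size paragraph pairs 23 per group with a difference of 3 curls, but 23 belongs to 3.4 curls (20% of 17); by the same formula 3 curls needs 30 per group

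*Protocol article*

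**What the plan says.** The Sample size section of the protocol article starts from the premise that pole walking should produce changes at least 20% larger than regular walking on selected Seniors Fitness Test items. It says that the arm curl needed the most participants of those items, so the arm curl sets the number. The norm is given as "for the arm curl test (mean, 17, SD, 4.1"), with "a power of 0.80 and significance of 0.05", and the number is obtained "using the formula n = 2[z*s^2^/Δ^2"]. The conclusion is that "23 participants per group would be needed to detect a between group difference of 20% (i.e. mean, 3, SD, 4.1) in the change score".

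The Randomization section plans more than that: "the total number will be approximately 30 participants in the PW group and 30 in the RW group".

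The calculation does not say whether the test is one-sided or two-sided. Two other places bear on this. In the Background, "The null hypothesis is that there is no difference in these outcomes between participants in the PW group and the RW group". In Data analysis, "The level of significance will be set at 0.05", with no direction given.

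**The concern.** One sentence gives two descriptions of the same target, 20% and 3 curls, and they differ. Twenty per cent of 17 is 3.4, while 3 curls is 3/17 = 17.6%. The difference enters the formula squared, so this changes the required number by a factor of (3.4/3)² = 1.28.

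A sample size statement tells the reader which difference the trial can detect. Read literally, this one says that 23 analysed participants per group are enough to detect 3 curls with 80% power. Anyone who later uses 3 curls as the target, for instance to interpret a confidence interval or to judge whether losses have left enough participants, would be working from a pairing that the protocol's own formula does not support.

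**Working it through.** **Inputs, all from the Sample size section unless noted**
- Norm for the arm curl: mean 17, SD s = 4.1. The SD is applied to the change score, as the protocol does.
- Power 0.80, significance 0.05.
- Sidedness: not stated. Two-sided is assumed, because the Background sets a null of no difference.
- Difference Δ: 20% of 17 = 3.4, or 3 as printed.
- Equal groups, about 30 planned in each (Randomization).

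**Formula.** The protocol prints n = 2[z·s²/Δ²] without defining z. Reading z as (1.960 + 0.842)² = 7.849 gives the usual two-group formula. Reading z as 1.96 or 2.8 gives at most about 10 per group at either difference, so 7.849 must be what was meant.

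**Step 1: reproduce the stated 23.** With Δ = 3.4:
n = 2 × 7.849 × 4.1² / 3.4² = 22.83, so 23 per group. The stated figure is reproduced.

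**Step 2: use the printed difference.** With Δ = 3:
n = 2 × 7.849 × 4.1² / 3² = 29.32, so 30 per group. The stated figure is not reproduced.

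**Step 3: power.** By the normal approximation, power = Φ(Δ / (s√(2/n)) − 1.960).
- For n = 23, s√(2/n) = 1.209. At Δ = 3: Φ(2.481 − 1.960) = 69.9%. At Δ = 3.4: Φ(2.812 − 1.960) = 80.3%.
- For n = 30, s√(2/n) = 1.059. At Δ = 3: Φ(2.834 − 1.960) = 80.9%. At Δ = 3.4: Φ(3.212 − 1.960) = 89.5%.

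| Per group | Δ | Normal approximation | Two-sample t test |
|---|---|---|---|
| 23 | 3 | 69.9% | 68.0% |
| 23 | 3.4 | 80.3% | 78.5% |
| 30 | 3 | 80.9% | 79.6% |
| 30 | 3.4 | 89.5% | 88.5% |

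**Step 4: difference detectable with 80% power.** By the normal approximation this is 2.802 × s√(2/n): 3.39 curls with 23 per group and 2.97 with 30. By the t test it is 3.46 and 3.02.

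**Step 5: sensitivity to sidedness.** A one-sided test at 0.05 gives 23.10 at 3 curls, which is 24 rounded up and very close to the stated figure. At 3.4 curls it gives 17.98, so 18.

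**The case against.** **The 3 is only a rounded 3.4.** This is probably right. The section describes its target as 20% throughout and supplies the 17 and the 4.1 that lead exactly to 23. The calculation therefore stands. The sentence does not, because it offers 3 as the meaning of 20%, gives the SD beside it to one decimal, and the rounding moves the required number from 22.8 to 29.3.

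**The trial enrols about 30 per group anyway.** This stands, and it limits the consequence. A reader might infer from the 68% figure that the trial is underpowered. The documents do not support that: 68% combines the printed 3 curls with 23 per group, and 23 is not the planned size. With 30 per group analysed, power is about 80% at 3 curls and 88% to 89% at 3.4.

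**A dropout cushion is lost.** A reader might also take the step from 23 to 30 as an allowance for dropout that vanishes at 3 curls. The protocol never calls it one. The Randomization section arrives at about 30 per arm from four sites and the size of the walking groups. The section on attendance and dropout also provides for carrying the last measure forward. How that fits with an intention-to-treat set limited to people with follow-up data is a separate question.

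**A one-sided test would rescue 23 at 3 curls.** Nearly so (23.10). It is therefore too strong to say that 23 can arise only from 3.4 curls, unless a two-sided test is assumed. Nothing in the protocol indicates a one-sided test, and at a true 20% a one-sided test would give 18, so the sentence would still be inconsistent.

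**A t test would ask for 24 or 31.** These figures (23.8 and 30.3, rounded up) reflect a different convention. The protocol declares a normal-approximation formula, under which 23 is correct for 3.4 curls and 30 for 3 curls.

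**The planned analysis is covariate-adjusted.** If baseline were a covariate, which the protocol does not say, and 4.1 were the outcome SD, the required number would shrink by (1 − r²). At an assumed r = 0.5, 3 curls would need 29.32 × 0.75 = 22 per group. The power figures above may thus be pessimistic for the final analysis. This does not reconcile the sentence, whose formula contains no such term.

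**Conclusion.** The point holds as a reporting inconsistency. Assuming a two-sided 0.05 test and SD 4.1 for the change score, the stated 23 per group matches 3.4 curls. The printed 3 curls needs 30 per group by the same formula, and 23 would give about 68% to 70% power. That 3 is a rounded 3.4 is the most likely explanation, though the text does not confirm it. The planned trial has no power deficit at the 20% target. At 3 curls it has about 80% power if all 30 per group are analysed. The weight is minor to moderate.

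**What to change.** Make the sentence consistent in one of two ways:
- print the difference as 3.4 curls and keep 23 per group; or
- keep 3 curls, state 30 per group, and stop calling it 20%, since it is 17.6% of 17.

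The first matches the rest of the paragraph and leaves the calculation unchanged. Either way, state that the test is two-sided.

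Optionally, add the difference that the planned 60 participants can detect with 80% power: about 3.0 curls if all 30 per group are analysed, and about 3.4 to 3.5 if 23 per group remain.

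The cost is a sentence or two of wording. Enrolment, design and analysis do not change.

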### Randomization

After baseline assessment of eligible participants at one site, the lead researcher will notify an external researcher of the participant identification numbers. The external researcher will randomly assign 50% of the participants to the PW intervention and 50% to the RW intervention using a random number generator in SPSS and inform the lead researcher of group allocation. This process will be repeated for each site separately. Thus, the total number will be approximately 30 participants in the PW group and 30 in the RW group, with one PW group, and one RW group, with seven to eight participants in each group, at each of four sites.

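### Randomisation is stratified by site, but the analysis section does not name site and its covariate rule is unlikely to select it

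*Protocol article*

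**What the plan says.** The protocol article describes the setting this way: "Participants will be recruited from four senior living facilities at different locations, but with similar environmental characteristics" (Study sample and recruitment). Under Randomization, once baseline assessment at a site is complete, an external researcher will "randomly assign 50% of the participants to the PW intervention and 50% to the RW intervention". The section continues: "This process will be repeated for each site separately". The expected result is "approximately 30 participants in the PW group and 30 in the RW group", made up of one pole-walking and one regular-walking group at each facility, "with seven to eight participants in each group, at each of four sites".

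Under Data analysis, the between-arm comparison is a repeated-measures analysis of covariance, "adjusted for variables that are associated with both the explanatory and outcome measures". The examples given are open-ended: "these may include factors such as age, sex and number of medical conditions". Neither site nor facility appears in that section.

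**The concern.** A factor used to restrict randomisation normally belongs in the analysis model. The restriction removes site differences from the arm comparison. A model without site still counts those differences as residual noise, so the reported standard error does not reflect the precision the design achieved.

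The article also fixes a selection rule that works against including site. Requiring association with the explanatory measure, here arm, is how confounders are screened in an observational study. Site is split about evenly between arms by construction, so it is unlikely to meet that condition however strongly it predicts change. At stake are confidence intervals that are too wide and a modest loss of power in a trial of about 60 people. There is also an avoidable choice about site left open until the data are seen.

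**Working it through.** **Inputs from the protocol article.** Four sites, seven to eight per arm per site, about 30 per arm (Randomization). Arm-curl mean 17, SD 4.1 used for the change score, power 0.80, significance 0.05, 23 per group (Sample size). A two-sided test is assumed, as sidedness is not stated.

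**The plan's own figure.** n per group = 2 × SD² × (1.960 + 0.842)² / Δ².
- Δ = 20% of 17 = 3.4: n = 22.83, rounded up to 23. This reproduces the stated number.
- Δ = 3, the value printed: n = 29.32, rounded up to 30.

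The mismatch between 3 and 3.4 is a separate matter, so both differences are carried below.

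**Assumption.** The article gives no between-site variance. Let ρ be the share of change-score variance lying between sites, taken as 0 to 0.30, with total SD held at 4.1.

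**Why the standard error is too large.** With site balanced across arms, the variance of the arm difference depends essentially on the within-site part, (1 − ρ)SD². Without site in the model, the expected residual variance is about SD² × [(1 − ρ) + ρ × 15 × 3/58], because four sites of 15 put 15 × 3 = 45 units of between-site variance into a residual with 58 degrees of freedom. The ratio of reported to true standard error is therefore √{[(1 − ρ) + 0.776ρ]/(1 − ρ)}:
- ρ = 0.05: √(0.9888/0.95) = 1.02
- ρ = 0.10: √(0.9776/0.90) = 1.04
- ρ = 0.20: √(0.9552/0.80) = 1.09

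**Simulation.** 4 sites × 15 participants (8/7 or 7/8 per arm), change score analysed by least squares without and with site as a fixed effect, 40,000 trials per cell, no walking-group variance. Entries are without site → with site.

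| Site share ρ (assumed) | Type I error | Power, Δ = 3 | Power, Δ = 3.4 |
|---|---|---|---|
| 0 | 0.050 → 0.050 | 0.795 → 0.794 | 0.886 → 0.884 |
| 0.05 | 0.045 → 0.048 | 0.806 → 0.815 | 0.894 → 0.900 |
| 0.10 | 0.043 → 0.051 | 0.813 → 0.833 | 0.900 → 0.912 |
| 0.20 | 0.036 → 0.051 | 0.834 → 0.875 | 0.913 → 0.939 |
| 0.30 | 0.030 → 0.051 | 0.850 → 0.910 | 0.926 → 0.964 |

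Power rises down the columns only because total SD is fixed, so a larger site share leaves less within-site variance. The comparison that matters is across the arrow. Separate runs agree closely: type I error without site at ρ = 0.05 lies between 0.045 and 0.047, and the cost of adding site at ρ = 0 is 0.1 to 0.3 points. Simulation error on a rate near 0.05 is √(0.05 × 0.95/40,000) ≈ 0.001. Adding site takes residual degrees of freedom from 58 to 55.

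**Allowing the eight walking groups their own variance (assumed shares).** Type I error, without → with site:
- 0% site, 5% group: 0.090 → 0.094
- 10% site, 5% group: 0.082 → 0.096
- 10% site, 10% group: 0.122 → 0.144

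**The case against.** Four objections have force.

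**The list is open.** A reader might infer that the plan excludes site, or that site can never qualify. The text supports neither. The examples are illustrative, the article is condensed, and an analysis plan that is not shown may name site. Odd numbers at a site, or uneven loss to follow-up, could also create some imbalance between site and arm. What stands is narrower: the article prints a selection rule, and that rule is unlikely to select site.

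**Baseline differences largely cancel.** It is tempting to say that every difference in case mix between facilities stays in the residual. In a before-after analysis, differences in starting level mostly drop out, and only site differences in change matter. The article describes the facilities as environmentally similar, and nothing in it supports a share as large as 20%. On the other side, routes are common to both arms within a site, and sessions are held beside each facility under therapists the residents know (Intervention). Some site difference in change is therefore plausible.

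**The test need not be conservative.** A reader might conclude that omitting site at least errs on the safe side. That holds only if the walking groups contribute no variance. With even a 5% group share, type I error exceeds 0.05 in both models and is slightly higher with site included. This objection stands in full and limits what the fix can claim.

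**The effect is small.** This also stands. At 5% to 10%, the loss is about 1 to 2 points at a difference of 3, and the estimate itself is unbiased.

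**Conclusion.** The point holds as a minor one, about efficiency and prespecification. The trial randomises within site, while the stated analysis does not name site and uses a rule unlikely to bring it in. If sites differ in change and walking groups add no variance of their own, standard errors are about 2% to 9% too large for assumed site shares of 5% to 20%. Type I error is then about 0.047 to 0.036, and about 1 to 4 points of power are lost at a difference of 3. If sites do not differ, including site costs at most about 0.3 points.

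The direction follows from the design. The size rests wholly on the assumed shares and on using the SD of 4.1 for change. The documents do not support reading this as bias in the treatment effect or as a formal exclusion of site. They also give no assurance that the unadjusted test is conservative.

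**What to change.** In the Data analysis section, state that site (four levels) is a prespecified fixed effect in every between-arm model for primary and secondary outcomes, because allocation was made separately within each site, and that it is kept whatever its observed association with arm. The covariate rule would then apply, if at all, only to other variables.

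The cost is one sentence and 3 degrees of freedom. Enrolment, data collection and the stated 23 per group do not change. The sentence should not be presented as dealing with correlation within the eight supervised walking groups, which needs its own treatment.
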